### Design

Two designs are combined: a single-case experimental design (SCED) and a repeated measures (RM) design. Given the vulnerable and highly specific population of patients with severe EDs, a SCED was considered more feasible and ethically appropriate than, for example, a randomized controlled trial, as it reduces the number of participants required and avoids withholding treatment from a control group.

A SCED multiple baseline design differentiates between time and intervention effects, with participants serving as their own controls. Experimental control is demonstrated when changes in outcome variables occur consistently after the introduction of the intervention across staggered baselines. Replication of this pattern across participants strengthens causal inference regarding intervention effects. The number of baseline measurements is randomized (ie, the number of measurements before the start of the intervention), varying from 5 to 8 weeks (ie, 5‐8 measuring points). Weekly measurements are taken for the duration of the assigned baseline plus the length of the intervention. The Eating Disorder Examination Questionnaire–Short (EDE-QS) [36] and the ACS-30-ST measure short-term ED symptoms and autonomy-connectedness characteristics, respectively.

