### Participants

Participants will be 22 to 30 patients (aged 18‐65 years) at the Center for Eating Disorders, GGZ Oost Brabant, Helmond, the Netherlands, in the last phase of multidisciplinary ED treatment, where treatment focuses on consolidating recovery, facilitating the transition to outpatient care or treatment completion, promoting self-management, and preventing relapse.

Prior to this last phase of treatment, participants will have completed 9 to 12 months of day care treatment for AN or BN, consisting of 2, 3, or 5 days of group therapy every week, including psychotherapy, sociotherapy, psychomotor therapy, drama therapy, and supported meals and snacks. All participants will have a BMI higher than 18.5 kg/m^2^.

All patients moving into the last phase of treatment are eligible for participation in this study. Inclusion and exclusion criteria for this study are therefore identical to the criteria for moving into the last phase of treatment. Eligibility for moving into the last phase of treatment is determined by the multidisciplinary treatment team. Patients enter this phase when ED symptoms are considered to be in remission at a behavioral level, allowing treatment to shift from symptom reduction toward maintaining recovery gains and preventing relapse. Main reasons for not progressing to the last phase include patients finding treatment closer to home, patients requiring specific care for posttraumatic stress disorder, autism, or personality disorders, or patients dropping out of treatment after failing to adhere to day care weight gain requirements.

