### Procedures

All patients in day care ED treatment at GGZ Oost Brabant are informed about the study by the main practitioner and the principal investigator, both orally and in written form. Before deciding to participate, patients have opportunities to ask questions and have 2 weeks to consider participation. Those who agree to participate fill out an informed consent form on paper. Each set of 4 participants is randomly allocated without replacement to a baseline length of 5, 6, 7, or 8 weeks, using a predetermined random list of 150 numbers generated using statistical software by an independent person in the presence of the main investigator. To start participants on their baseline measurements on time, main practitioners are asked to estimate when patients are likely to move on to the last phase of treatment. When participants have started baseline measures but need more time in day care treatment, baseline measures are paused until they are close to moving on.

When participants have started baseline measures but choose not to continue into the last phase of treatment, their allocated baseline number is placed back on top of the list.

All questionnaires are answered digitally on any device. Weekly measures will take approximately 10 minutes; 3-monthly measures will take approximately 30 minutes. Questionnaire invitations as well as reminders are sent by email.

Posttreatment interviews will take place at the GGZ facility or online, conducted by the investigator and guided by a topic-list. Interviews are audio-recorded and later transcribed.

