Because autonomy-enhancing therapy is embedded in treatment as usual (TAU) during the last phase of treatment, participants will receive 12 to 24 weeks of autonomy-enhancing therapy (Figure 1), ensuring that each patient covers every theme at least once and at most twice. As this study investigates the real-life application of autonomy-enhancing therapy in ED aftercare, all patients will also continue to receive TAU for the last phase of treatment, consisting of drama therapy, psychomotor therapy, and regular group therapy. TAU focuses on consolidating recovery gains, preventing relapse, and supporting the transition to everyday life.

Therapists providing autonomy-enhancing therapy are trained and certified in the autonomy-enhancing therapy protocol through RINO Amsterdam, a Dutch postgraduate training institute for mental health professionals. As part of maintaining certification, therapists participate in regular intervision meetings in which treatment delivery and adherence to the protocol are discussed. Formal assessment of treatment fidelity is not conducted within the present study. No major risks beyond regular treatment are expected. Any adverse psychological events, treatment deterioration, or participant withdrawal related to study participation will be discussed within the clinical treatment team and documented.

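### The baseline-to-treatment contrast combines the therapy with a partial, readiness-timed change of program, so staggered baselines cannot show the effect of the therapy alone

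*Protocol article*

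**What the plan says.** The Design section makes a causal claim for the multiple baseline: "A SCED multiple baseline design differentiates between time and intervention effects, with participants serving as their own controls". It adds that "Experimental control is demonstrated when changes in outcome variables occur consistently after the introduction of the intervention across staggered baselines". The randomized element is the length of the baseline: "The number of baseline measurements is randomized (ie, the number of measurements before the start of the intervention), varying from 5 to 8 weeks".

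Other sections describe what happens at the boundary between baseline and treatment.

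- **Timing of the move (Participants).** "Eligibility for moving into the last phase of treatment is determined by the multidisciplinary treatment team". The criterion is close to the primary outcome: "Patients enter this phase when ED symptoms are considered to be in remission at a behavioral level".
- **Timing of the baseline (Procedures).** So that baseline starts on time, "main practitioners are asked to estimate when patients are likely to move on to the last phase of treatment". If participants have started but "need more time in day care treatment, baseline measures are paused until they are close to moving on".
- **Care after the move (Intervention).** The therapy is embedded in the last phase and lasts 12 to 24 weeks; the last phase lasts 3 to 6 months. Besides the therapy, "all patients will also continue to receive TAU for the last phase of treatment, consisting of drama therapy, psychomotor therapy, and regular group therapy".

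Under Analyses, the primary hypothesis is tested with a single dummy, coded 1 in either treatment period and 0 in baseline. The limitations in the Discussion say that usual treatment given alongside makes unique attribution difficult. They do not say that usual treatment itself changes at the phase boundary, and they do not mention the pause.

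**The concern.** A multiple-baseline design supports a causal reading when the intervention is what changes at the phase boundary and when the timing of that boundary does not depend on the participant's state. Both conditions are in doubt here. The participant also moves from one program to another, and the team times the move by its judgment of remission.

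Usual treatment that stayed the same in both phases would largely cancel in a within-person comparison. Usual treatment that changes at the boundary does not cancel. At stake is what a positive or negative primary result can be said to show: an effect of the therapy, or a change seen on passing from late day care to a last-phase program that includes it.

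**Working it through.** **1. The two phases side by side** (Participants and Intervention sections)

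| Element | Baseline weeks: day care | Treatment weeks: last phase |
|---|---|---|
| Intensity | 2, 3 or 5 days of group therapy a week | days per week not given |
| Psychotherapy, sociotherapy | listed | not listed under these names |
| Supported meals and snacks | listed | not listed |
| Drama and psychomotor therapy | listed | listed |
| Group therapy | listed | listed |
| Autonomy-enhancing therapy | not part of it | 12 to 24 weeks |
| Focus | symptom reduction | consolidation, relapse prevention, transition |

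The change of care is real but partial.

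**2. Does the therapy start with the program?** Its 12 to 24 weeks match the 3 to 6 months of the last phase. New members begin with whichever theme is scheduled that week, and the therapy ends at discharge. No therapy-free stretch of the last phase is described. A simultaneous start is therefore the natural reading, but no single sentence states it.

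**3. What the randomization fixes.** Let D be the date of the move and b the allocated baseline length (5 to 8). Baseline start is planned at about (expected D) minus b weeks. The lottery therefore sets how many measurements precede the move, while the treatment team sets D. Staggering gives look-backs of different length before the same kind of clinical event. The text does not say whether a move ever waits for a baseline to finish.

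**4. What the dummy estimates.** Let L = 1 in the last phase and A = 1 when receiving the therapy. If both start together, L = A = P (the phase dummy) in every record, and

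β_L·L + β_A·A = (β_L + β_A)·P.

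Only the sum can be estimated. More participants or a different covariance model do not change that.

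**5. The plan's own figures** (Analyses section). For a single coefficient, two-sided α = .05, f² = 0.15 and 7 predictors, take df = N − 8 and noncentrality √(0.15·N). Power reaches 0.95 at N = 89, as stated. Effective observations per participant are 20/(1 + 19 × 0.2) = 4.17, and 89/4.17 = 21.4, so 22 participants. With 30 participants, 30 × 4.17 = 125 and power is 0.99. These reproduce, but they concern precision, not what is being estimated.

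**6. Illustration of size.** The planned model was simulated with the phase dummy, a common linear slope centered within period, a random intercept and first-order autoregressive errors.

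- From the protocol: ICC 0.2, 5 to 8 baseline weeks, 1-tailed .05, 22 or 30 participants.
- Assumed: 12 treatment weeks (the minimum), known covariance, autocorrelation 0 or 0.3, and the size of the switch effect in within-person SD.
- The true therapy effect is zero. There were 4,000 runs per setting.

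| Improvement from the switch alone | Mean of the dummy | Significant, 22 participants | Significant, 30 participants |
|---|---|---|---|
| 0 | 0.00 | about 5% | about 5% |
| 0.1 | −0.10 | 19-24% | 22-31% |
| 0.2 | −0.20 | 45-61% | 55-72% |
| 0.3 | −0.30 | 74-88% | 86-96% |

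The opposite case follows from step 4. If the therapy truly gives −0.3 and leaving day care gives +0.2, the sum is −0.1. The chance of significance then falls from 74-88% to 19-24% with 22 participants, and from 86-96% to 22-31% with 30.

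**7. The pause.** If measurements were indexed by order instead of date, two readings separated by g skipped weeks would be given correlation ρ in place of ρ^(g+1). With ρ = 0.3 and g = 3 (both assumed), that is 0.3 in place of 0.3⁴ = 0.008. The linear time term would be compressed in the same way. The article does not say which index is used or how many participants were paused.

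**The case against.** The best case for the plan is that it is a real-life study of an embedded therapy and largely says so. The Discussion concedes that unique attribution is difficult, the abstract lists the absence of a control condition as a limitation, and controlled trials are left to later work. Drama, psychomotor and group therapy occur in both programs. Details of time indexing and sensitivity analyses are commonly left to an analysis plan. All of this stands, and it narrows the point. It does not cover the change of usual treatment at the boundary or the readiness-based timing, and the causal sentences in the Design section are unqualified.

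Several stronger readings are tempting but not supported:

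- **That the whole phase contrast is known to be confounded.** The simultaneous start is inferred, and Figure 1 is not available to confirm it.
- **That the bias favors the therapy.** Losing supported meals and intensity could worsen scores. Leaving out weeks with higher symptoms would lower the baseline and work against finding a decrease.
- **That the pause removes all not-ready weeks.** Measurements taken before the pause are not said to be discarded.
- **That the Discussion and the abstract claim to isolate the therapy.** As a strength of the single-case design, they claim only insight into the treatment process. The causal wording about experimental control is in the Design section.
- **That every pre-therapy week should become the main baseline.** That would let readiness set the baseline length and discard the one randomized element.

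**Conclusion.** The point holds in a limited form. On the natural reading of the protocol, the primary dummy estimates the therapy plus a partial change of program, at a time set by clinical readiness. The Design section's claim to differentiate intervention from time effects therefore does not hold for autonomy-enhancing therapy on its own. The stated limitation about concurrent usual treatment does not reach this.

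The size is unknown. Any effect of the switch enters the estimate in full and in its own direction. The percentages above show only that modest shifts of 0.1 to 0.3 SD would matter at this sample size; the shifts and the autocorrelation are assumptions. The conclusion rests on the therapy starting with the last phase. If Figure 1 or the full protocol shows a therapy-free period there, it would need to be revisited. This should be corrected before results are interpreted; it does not make the study uninformative.

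**What to change.** 1. **Design section.** Limit the claim of experimental control, and state the primary contrast as the last-phase program including autonomy-enhancing therapy versus late day care.
2. **Limitations.** Add that usual treatment changes at the phase boundary, that readiness sets the move and hence the baseline start, and that baselines may be paused for the same reason. Say that the direction of any resulting bias is unknown.
3. **Main analysis.** Keep the randomized 5 to 8 baseline measurements. Model the time term and the autoregressive error by actual measurement date, so that paused weeks count as elapsed time.
4. **Sensitivity analysis.** Report how many baselines were paused and for how long, and repeat the primary analysis without those participants.

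The cost is a weaker causal claim, some rewording and a little extra analysis using the dates of the digital questionnaires. Nothing in patient care or in the weekly measurement burden changes, and data collection is still open (projected to finish in February 2027).

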### Intervention

Autonomy-enhancing therapy’s goal is to enhance autonomy-connectedness at behavioral, attitudinal, and emotional levels by working on personal, autonomy-related goals.

The investigational treatment, autonomy-enhancing therapy, consists of 15 weekly 2-hour group sessions, following the existing autonomy-enhancing therapy protocol [21]. The autonomy-enhancing therapy protocol prescribes a mindfulness exercise, space to share progress toward personal autonomy goals, and the appointment of a chairperson for each session who, with therapist support, keeps time. Each week features different autonomy-related themes (eg, relationships, boundaries, body and sexuality, and emotions), including psychoeducation, exercises, homework, and discussion of autonomy-related difficulties. Autonomy-enhancing therapy groups typically consist of 8 participants (range 4‐10).

The autonomy-enhancing therapy protocol has been slightly adjusted to fit the existing structure of the last phase of treatment in the Center for Eating Disorders, GGZ Oost-Brabant, Helmond. In this phase of treatment, participants are part of a group that follows several treatment modules together. Relapse prevention is covered in standard treatment, so introductory, relapse prevention, and midpoint evaluation sessions are omitted, leaving 12 sessions. Additionally, new members continuously join the group in the last phase of treatment, so patients start with whatever theme is planned for that week, ensuring that all themes are covered, even if the starting point varies. In the last phase of treatment, patients participate for a minimum 3 to maximum 6 months, with continuation decided after an evaluation at 3 months. Continuation or discharge is determined by main practitioners, guided by input from the treatment team. Participation in the intervention stops when individuals are discharged. After finishing their ED treatment, many patients proceed to other forms of treatment (eg, trauma treatment, treatment focused on personality disorders, or general psychological support).

Because autonomy-enhancing therapy is embedded in treatment as usual (TAU) during the last phase of treatment, participants will receive 12 to 24 weeks of autonomy-enhancing therapy (Figure 1), ensuring that each patient covers every theme at least once and at most twice. As this study investigates the real-life application of autonomy-enhancing therapy in ED aftercare, all patients will also continue to receive TAU for the last phase of treatment, consisting of drama therapy, psychomotor therapy, and regular group therapy. TAU focuses on consolidating recovery gains, preventing relapse, and supporting the transition to everyday life.

Therapists providing autonomy-enhancing therapy are trained and certified in the autonomy-enhancing therapy protocol through RINO Amsterdam, a Dutch postgraduate training institute for mental health professionals. As part of maintaining certification, therapists participate in regular intervision meetings in which treatment delivery and adherence to the protocol are discussed. Formal assessment of treatment fidelity is not conducted within the present study. No major risks beyond regular treatment are expected. Any adverse psychological events, treatment deterioration, or participant withdrawal related to study participation will be discussed within the clinical treatment team and documented.

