**Conclusions:**

This study addresses the need for improved ED treatments by investigating autonomy-enhancing therapy as a potentially valuable adjunct to existing care. Targeting autonomy-connectedness may contribute to reductions in ED symptoms, as well as to broader psychological recovery. Strengths of this study include its practice-based design and the use of a single-case experimental design, allowing a detailed examination of treatment processes. Limitations include the absence of a control condition and the limited follow-up period, which may not fully capture relapse during the period of highest relapse risk. If promising, this study may provide a foundation for future larger-scale controlled studies on autonomy-enhancing therapy in ED treatment.

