### Analyses

Sample size and statistical power were approximated using G*Power (version 3.1.9.4). To detect a medium effect size (*f*^2^=0.15) in a regression with 7 predictors, 89 independent observations are needed for a power of 0.95 at α=.05. For the SCED analysis, with an intraclass correlation coefficient of 0.2, each participant’s 20 observations yield 4.17 independent observations [45], necessitating at least 22 participants. To ensure robustness, we aim for 30 participants (125 independent observations), achieving a power of 0.99. Considering a 20% dropout rate, we plan to recruit 36 participants. For the RM analysis, assuming 3 observations per participant, we obtain 30×2.14=64 independent observations, resulting in a power of 0.67 to detect a medium effect size (using α=.01).

Differences between individuals in their SCED data will be examined using visual analyses, presenting separate plots for all participants’ measures [46]. Visual analysis will evaluate changes in level, trend, variability, immediacy of effect, overlap between phases, and consistency across participants. Interview data will be used descriptively to better understand participants’ experiences of the intervention and their interpretation of change. The interview data will be reviewed and summarized to identify recurring experiences, perceived benefits and challenges, and considerations relevant to feasibility and future implementation.

The SCED data will be analyzed using a mixed model with 2 treatment periods, incorporating 2 dummy variables (treatment period 1 and treatment period 2, with baseline as the reference). A linear effect of time, centered within each period, represents the average change across periods. A random intercept and an autoregressive error structure will model the covariance structure. The primary hypothesis of the average decrease in ED symptoms is tested with 1 dummy for treatment period (1=treatment period 1 or 2, 0=baseline). This hypothesis will be tested for autonomy-connectedness.

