The RM data for all outcome variables will be analyzed using mixed models. Measurement will be modeled with 3 dummy variables (after treatment period 1, after treatment period 2, and after 3 months, all with baseline as the reference category), and an unstructured covariance matrix will model the random effects. The analyses will focus on the effect of dummy “post,” testing the hypothesis that scores improve compared with baseline. Mediation by autonomy-connectedness will be tested in two steps: (1) adding autonomy-connectedness to the model and (2) conducting a dependent-samples *t* test (1-tailed) comparing autonomy-connectedness after treatment and at the 3-month follow-up with baseline. Mediation will be concluded if (1) autonomy-connectedness affects the outcome variable in the mixed model analysis and (2) autonomy-connectedness improves over time in the *t* test, indicating a joint-significance test of mediation [47].

All analyses will control for ED diagnosis (dummy AN, with BN as the reference category). We will explore whether the development over time of ED, autonomy-connectedness, and the other outcome variables differ between the two EDs.

Hypotheses on change will be tested 1-tailed, with a significance level of .05 for the multiple baseline data and .01 for the RM data to correct for multiple testing. Missing values on the outcome variable do not affect mixed model analyses [45], whereas participants with missing autonomy-connectedness values will be excluded from the mediation analyses.

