Several limitations should also be considered. First, participants will continue to receive TAU alongside autonomy-enhancing therapy, making it difficult to determine whether observed changes can be uniquely attributed to autonomy-enhancing therapy. However, because autonomy-enhancing therapy is intended as an adjunctive intervention integrated into routine clinical care, studying it within the context of ongoing treatment may also increase the clinical relevance of the findings. Second, the relatively small sample size may limit generalizability. Third, highest relapse risk is reported to occur approximately 4 to 6 months after treatment, whereas the current study includes a follow-up assessment at 3 months after treatment due to feasibility constraints. This study may therefore not fully capture relapse during the period of highest risk. Finally, recruitment and adherence may prove challenging due to the repeated weekly measures.

Future research should further examine the effectiveness of autonomy-enhancing therapy in larger and more diverse ED populations, investigate long-term outcomes, and examine effects on relapse. If the present study yields promising findings, future studies could include larger controlled trials to further evaluate efficacy.

The findings of this study will be disseminated through peer-reviewed publications and presentations at scientific conferences, as well as at practice-oriented conferences for clinicians working in ED treatment. In doing so, we aim to contribute to the development of more comprehensive and relapse-sensitive approaches to ED treatment.

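### Withdrawal, and on a natural reading deterioration and adverse events too, is documented only if related to study participation, so participants who relapse and leave can be missing from the event record

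*Protocol article*

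**What the plan says.** The Intervention section of the protocol article states the rule: "Any adverse psychological events, treatment deterioration, or participant withdrawal related to study participation will be discussed within the clinical treatment team and documented". It gives no criterion for relatedness and does not say who judges it.

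On attribution, the abstract's Conclusions state: "Limitations include the absence of a control condition and the limited follow-up period". The Discussion says that usual treatment runs alongside the therapy, "making it difficult to determine whether observed changes can be uniquely attributed to autonomy-enhancing therapy". The Design section also claims some own-control strength: "A SCED multiple baseline design differentiates between time and intervention effects, with participants serving as their own controls".

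On symptom data, the Design section says: "Weekly measurements are taken for the duration of the assigned baseline plus the length of the intervention". The Intervention section says that participation in the therapy ends at discharge. The EDE-Q is collected at the start, middle and end of the intervention and 3 months later. The Analyses section plans a separate plot for every participant, judged on level, trend and other features without a fixed direction. Under Participants, patients enter this phase once their symptoms are judged to be in behavioral remission.

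**The concern.** Participants enter in remission, so relapse is the harm that matters most in this phase. A rule that documents an event only when it is related to the study requires a causal judgment before the event is written down. That judgment is hard here: the therapy and the usual treatment of the last phase run together, and there is no untreated group for comparison.

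A participant whose eating disorder returns and who then leaves may be seen as following the course of the illness. Under the stated rule, that exit need not be documented. If it is not, a reader of the final report cannot tell how many people left because they got worse.

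**Working it through.** The plan gives no figure on this point, so there is none to reproduce. The check sets the passages side by side and then illustrates the possible size.

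**1. What the qualifier covers.** The sentence allows two readings.

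| Event | Qualifier applies to all three | Qualifier applies to withdrawal only |
|---|---|---|
| Adverse psychological event | only if related | always documented |
| Deterioration | only if related | always documented |
| Withdrawal | only if related | only if related |

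Withdrawal is filtered in both columns.

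**2. What other data would show.**

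- *Worsens and stays:* the weekly EDE-QS, the 3-monthly EDE-Q and the individual plot all show it, whatever its cause.
- *Worsens and withdraws:* the scores up to the exit are kept. The article does not say whether questionnaires continue afterwards. If they stop, only the event record can show what happened. The first reading filters both the deterioration and the exit; the second filters the exit only.
- *Worsens after discharge:* weekly measurement has ended and one assessment remains at 3 months. The EDE-Q looks back 28 days, or 4 weeks. The article equates 3 to 6 months with 12 to 24 weeks, so about 12 − 4 = 8 weeks after discharge fall outside that window.

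The Analyses section adds that missing outcome values do not affect the mixed models, so nothing there prompts a look at why the data stopped.

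**3. Possible size (assumed rates).** Let n = 30 (the article's target), r = the share who worsen, and q = the share of those judged related. Expected documented events = n·r·q. With independent participants, the chance that none is documented = (1 − r·q)^n.

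| r (assumed) | q = 1 (all counted) | q = 0.5 | q = 0.25 | q = 0.1 |
|---|---|---|---|---|
| 10% | 3.0; 0.04 | 1.5; 0.22 | 0.75; 0.47 | 0.3; 0.74 |
| 22% | 6.6; 0.001 | 3.3; 0.03 | 1.65; 0.18 | 0.66; 0.51 |
| 51% | 15.3; 0.00 | 7.65; 0.00 | 3.8; 0.02 | 1.5; 0.21 |

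Each cell gives expected documented events, then the chance of none. The 22% and 51% are the relapse range cited in the article's Background, borrowed here as an assumption. They are not rates for the therapy phase. A reported zero in 30 would suggest a 95% upper limit of 1 − 0.05^(1/30) = 0.095, or 3/30 = 10% by the rule of three. That limit has no meaning if events were screened out first.

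**4. A remedy that would fail.** One could count participants with any week worse than their own baseline range. With no true change and exchangeable scores without ties, the chance that the highest of all weeks falls in treatment is m/(m + b), for m treatment and b baseline weeks. For b = 8 and m = 12 this is 12/20 = 60%. For b = 5 and m = 24 it is 24/29 = 83%. Ties and autocorrelation would change these values, but most stable participants could be labelled worse.

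**The case against.** The strongest reply is that this is one summary sentence in a journal article, and the full protocol may hold complete safety procedures. That stands as far as missing detail goes: only the published wording can be faulted. The wording still states a condition for documentation, and that condition is the problem.

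A reader might infer more than the documents support:

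- *That relapses during therapy go unseen.* They do not, for participants who stay. Symptom scores are collected from everyone with no relatedness condition.
- *That benefit counts whatever its cause while harm counts only if related.* On the primary outcome, a worsening score enters the same model estimate as an improving one and offsets it. The statement "Hypotheses on change will be tested 1-tailed" affects which results can be declared significant, not the estimate. It is a separate matter from what is recorded.
- *That the filter certainly applies to deterioration.* This is a natural reading, but the qualifier may attach to withdrawal alone.
- *That attribution is impossible.* The article calls it difficult. The randomized baseline lengths give some own-control basis, although they do not separate the therapy from usual treatment in the same phase.
- *That the treating team decides relatedness.* The article says that the team discusses these events; it does not say who classifies them.

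**Conclusion.** The point holds as a flaw in the event-recording rule. Withdrawal is filtered by relatedness on either reading, and deterioration and adverse events are filtered on a natural one, in a design for which the article concedes that attribution is difficult. The consequence is greatest for participants who relapse and then withdraw or are discharged, because their weekly scores end and their exit need not be documented.

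The documents do not support a claim that the efficacy estimates are biased by this rule or that worsening is hidden in those who stay. The size of the under-count cannot be stated. It depends on how many worsen and what share is judged related, and the article gives neither. The tabulated values show only that a filtered record could read zero when several events had occurred.

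**What to change.** Reword the sentence in the Intervention section along these lines:

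> Every adverse psychological event, deterioration, early discharge and withdrawal from the first baseline week to the 3-month follow-up is documented, whatever its presumed cause. The judged relation to study participation is recorded in a separate field.

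Report the counts descriptively for baseline, treatment period 1, treatment period 2 and follow-up. Show the number of participants in each phase, because the phases differ in length. Starting at the first baseline week matters because, under Procedures, a participant who starts baseline but chooses not to go on has the allocated baseline length returned to the list.

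Do not add a count of participants worse than their own baseline range unless a deterioration threshold is fixed in advance that allows for the unequal numbers of baseline and treatment weeks.

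The cost is one sentence, one extra field and a small table; the team is already meant to discuss these events. The event count may look slightly less favorable. Data collection is projected to run to February 2027, so the rule can apply prospectively to the 6 enrolled and 7 recruited participants. For the 18 who have completed, and for anyone who has already left, events would have to be reconstructed from existing records and marked as retrospective.
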